### Sample size

A patient record review from The Ottawa Hospital indicated that red blood cell transfusions were performed in approximately 60% of patients with bladder cancer undergoing radical cystectomy. However, we anticipate that transfusion rates are likely to decrease slightly while under the study protocol. From the results of our survey, systemic anti-fibrinolytics are rarely used during radical cystectomies; to influence practice we suggest that tranexamic acid will have to produce a substantial reduction in the proportion of patients requiring transfusion. To assist in determining the minimally important effect of tranexamic acid deemed necessary to change clinical practice, Canadian experts in the surgical treatment of bladder cancer were surveyed in February 2012. Minimally important effect sizes ranged from an absolute difference of 15% (relative risk (RR) 30%) to 30% (RR 60%) and are consistent with effects observed in many clinical trials of tranexamic acid [12]. From our systematic review of lysine analogs to prevent bleeding during pelvic surgery, the pooled estimate favored lysine analogs (RR 0.69; 95% confidence interval (CI) 0.47 to 1.00) [13].

If 50% of placebo patients will require at least one transfusion within 30 days of surgery, and if the use of tranexamic acid reduces the need for transfusion within 30 days to 35% of patients (15% absolute reduction), and assuming 80% power to detect this absolute difference, with a two-sided alpha level of 5%, the required sample size is 340 people (170 per treatment group). To account for 2% non-compliance with the protocol (possibly due to intraoperative complications or protocol deviations) the total sample size required was estimated to be 354 patients (177 per arm) [15].

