#### Blinding of intervention

Tranexamic acid, diluted in saline or undiluted, is clear, colorless, and indistinguishable from saline both at rest and when vigorously agitated [16]. Matching placebo maintenance infusions are identical saline bags without discarded saline or added drug in order to maintain the same volume and weight. To minimize sources of selection and ascertainment biases, anesthesiologists, surgeons, investigators, research staff, and members of the Data Safety and Monitoring Board (DSMB) are all blinded to randomization schemes and treatments administered; only the statistician has access to randomization schemes. The research pharmacist does not have contact with the study team or the patient, and is expressly forbidden to discuss individual treatment allocation with the operating room and clinical care team (a signed confidentiality agreement is obtained from each site research pharmacy personnel). Clinical teams are permitted to unmask treatment allocation only under exceptional circumstances. A request to unmask allocation for an individual patient is made to the coordinating center. A clinical member of the Executive Committee (24 h availability) reviews the request to ensure that it is necessary, based on pre-established criteria.

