### Statistical methods

Patient baseline characteristics will be summarized with descriptive statistics. Comparative analyses will be based on an intention-to-treat principle (i.e., based on the participant’s randomized study arm allocation). To address the primary objective of the effect of systemic tranexamic acid compared to placebo on the proportion of patients requiring red blood cell transfusion within 30 days, a chi-square test of proportions will be used. The effect size will be derived with an unadjusted RR and 95% confidence limits. If notable baseline imbalances are present, an adjusted estimate will be derived for the RR by stratifying on the potential confounders and pooling with a Mantel-Haenszel RR estimator. Secondary analyses of the effect of tranexamic acid on the volume of intraoperative blood loss and the perioperative adverse event rate will follow in a similar fashion, using chi-square or *t* tests, depending the outcome, and logistic or linear regression to estimate the magnitude of effect. A Poisson regression model will be fit to assess the difference in the number of transfused blood products between trial arms. Subgroup analyses will also be presented for clinically important baseline factors that may influence the effect of the drug, including sex, patient age (< 60 years, 60–70 years, 71–80 years, and < 80 years), preoperative hemoglobin (< 100 g/L, 100–120 g/L, and > 120 g/L), and previous history of cardiac disease (yes/no). Data is compiled by the study statistician and reviewed by an independent DSMB every 6 months. No interim analysis is planned for this trial.

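### The adjusted relative risk exists only if an undefined baseline imbalance appears; one prespecified adjusted analysis, reported whatever the balance, would be better

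*Protocol article*

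**What the plan says.** All of this is in the protocol article.

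- *Statistical methods*: the arms are compared on 30-day red cell transfusion by a chi-square test, with an unadjusted RR and 95% limits as the effect size. Neither depends on the data.
- *Statistical methods*, next sentence: "If notable baseline imbalances are present, an adjusted estimate will be derived for the RR by stratifying on the potential confounders", with the strata pooled by a Mantel-Haenszel RR estimator. No threshold or covariate list is given, and the text does not say how the adjusted RR ranks against the unadjusted one.
- *Statistical methods*, subgroups: sex, age (four bands), preoperative hemoglobin (three bands) and cardiac history are listed as "clinically important baseline factors that may influence the effect of the drug". They are named as possible effect modifiers, not as adjustment covariates.
- *Randomization*: 1:1, permuted blocks of 2, 4 and 6, stratified by center. Center is not mentioned in the primary analysis.
- *Sample size*: "If 50% of placebo patients will require at least one transfusion within 30 days of surgery" and tranexamic acid "reduces the need for transfusion within 30 days to 35% of patients (15% absolute reduction"; "the required sample size is 340 people (170 per treatment group") before the allowance for non-compliance.

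**The concern.** Leaving a covariate list to an analysis plan would be no fault. Here the protocol states a rule, and the rule is a poor one for three reasons.

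First, observed imbalance is the wrong trigger. With concealed randomization any imbalance is chance, and adjustment gains precision when a covariate predicts the outcome, whether or not the arms differ on it. Second, the rule makes the existence and content of the adjusted RR depend on arm-level baseline data, so readers cannot know beforehand which estimate they will be shown. Third, the randomization was stratified by center, yet neither the primary analysis nor the conditional one names center.

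At stake are the credibility of the supportive estimate and some power. The validity of the primary test is not in question.

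**Working it through.** **Inputs from the article.** Transfusion 50% against 35%; 80% power, two-sided 5%; 340 patients, then 354; 1:1 allocation stratified by center; 13 centers; four baseline factors with 2, 4, 3 and 2 categories.

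**Assumed, because the article gives no figure.** How strongly a baseline covariate predicts transfusion, the threshold for a notable imbalance, and the category shares.

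**1. The plan's own sample size.** With pooled variance, p̄ = 0.425:

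n per arm = [1.960·√(2·0.425·0.575) + 0.842·√(0.50·0.50 + 0.35·0.65)]² / 0.15² = (1.370 + 0.582)² / 0.0225 ≈ 169.3, so 170 per arm and 340 in all, as stated. 340 / 0.98² = 354.02, which matches 354. Power of the unadjusted test is 80.2% at 170 per arm and 81.7% at 177. The sizing is right, and it rests on the unadjusted test.

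**2. How often chance alone fires the trigger.** At N = 354 the standard error of a standardized difference is 2/√354 = 0.106. For one covariate, P(|difference| > 0.1 SD) = P(|Z| > 0.94) ≈ 35%. For four independent covariates, the chance that at least one fires is:

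- threshold 0.1 SD: 1 − 0.65⁴ ≈ 82%
- threshold p < 0.10: 1 − 0.90⁴ = 34%
- threshold p < 0.05: 1 − 0.95⁴ = 19%

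So an adjusted RR appears in anything from one trial in five to four in five, depending on a threshold that is not stated.

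**3. Power.** Simulation at N = 354, 50% against 35%; modified Poisson model with 13 centers and four covariates, one of them prognostic with the slope shown:

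| Log-odds slope per SD (assumed) | Unadjusted | Adjusted only if imbalanced | Always adjusted |
|---|---|---|---|
| 0 | 81–82% | 82% | 82% |
| 0.5 | 81–82% | 83% | 85% |
| 0.8 | 81–82% | 83% | 86% |
| 1.1 | 81–82% | 85% | 88% |

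At the top slope, always adjusting gains about 88 − 81 = 7 points and the trigger about 85 − 81 = 4.

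A second simulation at N = 340 used one covariate, logistic regression with standardization, and a trigger at p < 0.10 leading to three-band Mantel-Haenszel. Slopes of 0, 0.5, 0.8, 1.1 and 1.5 gave:

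- always adjusted: 80, 82, 84, 88 and 91%
- triggered: 80, 81, 81, 83 and 82%
- unadjusted: 80–82% throughout

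The largest gain from always adjusting is 91 − 80 = 11 points.

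**4. Type I error.** At N = 340 the planned chi-square test rejects in 4.1–5.0% of null trials. Counting success on either that test or any Mantel-Haenszel analysis triggered at p < 0.10 gives 4.6–5.3%. It reaches 8.5–10.8% only if any subset of the four factors may be picked regardless of balance, which the article does not allow.

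**5. Sparsity of Mantel-Haenszel strata.** Crossing the four named factors gives 2·4·3·2 = 48 cells, or 354/48 ≈ 7.4 patients each. Under assumed category shares, about 5.5% of patients then fall in cells holding one arm only, and about 12% of the information is lost. Crossing center (13) with hemoglobin and age gives 156 cells, about 2.3 patients each; roughly a quarter of patients are in one-arm cells and about two thirds of the information is kept. All five factors give 48·13 = 624 cells, about 0.6 patients each. With one three-band factor always applied, Mantel-Haenszel power was 82, 82, 85 and 88% for slopes 0.5 to 1.5, close to the model's 82, 84, 88 and 91%.

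**The case against.** The strongest reply is that nothing confirmatory is exposed. The test and the unadjusted RR are fixed unconditionally, the sample size is right for them, and extra precision from covariates is optional. All of that stands, and it rules out several stronger readings.

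- *Two competing primary RRs.* A reader might infer that the analyst may choose between them. Nothing in the text lets the adjusted RR replace the unadjusted one; the fault is that its rank is unstated.
- *Inflated type I error.* Reporting the better of two analyses when a 0.1 SD imbalance occurs gives about 5.4–6%, but the article states no such best-of-two rule.
- *Mantel-Haenszel breaks down.* It does so only when many factors are crossed, above all with center. Stratified blocks keep center close to balance, so it is unlikely to fire the trigger. For one or two factors the method is adequate.
- *Strong prognostic information is being discarded.* The article reports no association between any baseline factor and transfusion. *Primary outcome* does list serum hemoglobin among the inputs to transfusion decisions, which makes the preoperative value a reasonable candidate but says nothing of its strength.
- *An unblinded statistician picks the covariates.* *Blinding of intervention* says "only the statistician has access to randomization schemes", but no section says who judges balance. The sentence is context and not evidence of misuse.

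It may also be said that a threshold and a covariate list belong in an analysis plan that is not shown. That answers the missing details. It does not answer the rule itself, since defining the imbalance more exactly would leave it the wrong trigger. Nor is the trigger needed to guard against an unlucky imbalance, because an analysis that always adjusts already allows for it.

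**Conclusion.** The concern holds in a limited form. The primary test and unadjusted RR are prespecified and valid, and type I error under the plan as written is essentially intact. The adjusted RR is badly fixed: a chance event with no stated threshold decides whether it exists and for which factors, its rank is not given, and it recovers little of the precision available. The randomization stratum is not in the primary analysis.

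The gain from always adjusting is 0 to about 7 power points at 354 patients for assumed slopes of 0 to 1.1 per SD, and up to about 11 at a slope of 1.5 in the 340-patient simulation. The trigger yields roughly 0 to 4. These figures rest wholly on assumed prognostic strength. If the covariates predict nothing, the gain is nil and always adjusting costs essentially no power. This is an avoidable weakness that should be mended, not an invalid analysis.

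**What to change.** Delete the conditional sentence in *Statistical methods*. In its place, prespecify one adjusted RR, reported whatever the baseline balance: modified Poisson regression with robust standard errors, or logistic regression with standardization. Include treatment, center, continuous preoperative hemoglobin, continuous age, sex and cardiac history. State its rank; the unadjusted chi-square test may stay primary, with this as the single key supportive analysis.

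The cost is wording. The four patient factors are already needed for the subgroups and center is known from randomization. At the article's date 147 of 354 patients had been randomized, so the change could be made before any comparative analysis.

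There are two downsides. A model is less transparent than a two-by-two table. And with 12 center terms and about 177·(0.50 + 0.35) ≈ 150 expected events, the robust standard error may be slightly too small. Pool small centers by a rule set in advance, or use a small-sample correction.

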## Background

Bladder cancer is the sixth most common cancer in North America with an estimated 80,000 new diagnoses in 2011 [1, 2]. Among incident cancers it is estimated that 8% (6400 per year) will undergo radical cystectomy [3]. Radical cystectomy is an advanced surgical procedure that involves removal of the urinary bladder, adjacent organs, and pelvic lymph nodes. Removal of the urinary bladder also necessitates urinary reconstruction using an isolated segment of small or large intestine for urinary diversion. The extensive extirpative and reconstructive components of this surgery result in prolonged operative times and are associated with significant risk of complications including high risk of perioperative bleeding and subsequent need for blood transfusion [4]. Among individual surgeons at institutions that perform many procedures, median intraoperative blood loss is between 600 and 1700 mL [5–7]. The incidence of at least one intraoperative blood transfusion is 9 to 67% [5–9], and the postoperative transfusion risk is at least 15% [6, 9]. Among cystectomy patients who receive transfusion, a median of 2 units of blood cells are given [6, 9].

Lysine analog drugs are synthetic derivatives of the amino acid lysine that reversibly block lysine-binding sites on plasminogen molecules [10]. This action prevents the conversion of plasminogen to plasmin, the active enzyme that degrades fibrin clots. Therefore, lysine analogs decrease the breakdown of clots and are considered anti-fibrinolytics. There are two commonly studied lysine analogs, tranexamic acid and epsilon-aminocaproic acid. Both of these drugs have been shown to decrease blood transfusion need during some surgeries without a significant increase in adverse events.

In 2011, urologists who specialize in cancer treatment (members of the Society of Urologic Oncology) were surveyed about the methods they used to prevent blood loss during radical cystectomy [11]. Respondents were asked about their use of systematic techniques, systemic drugs, and topical agents to reduce blood loss and prevent blood transfusion. Topical agents were commonly used among expert urologists (73% used oxidized cellulose polymer; 53% used gelatin and thrombin matrix) and 28% used at least one systematic technique such as autologous blood recovery. Systemic drugs, such as lysine analogs, were used by only 5% of surgeons.

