#### Secondary outcomes

Secondary outcomes will assess other transfusion metrics and perioperative safety, cumulative to 30 days post operative. Documentation includes total units of red blood cells transfused, occurrence of postoperative bleeding requiring intervention (e.g., reoperation or angioinfarction), occurrence of platelet transfusion, total units of platelets transfused, occurrence of plasma transfusion, total units of plasma transfused, estimated intraoperative blood loss, and change in hemoglobin. Safety outcomes include occurrence of severe adverse events, such as DVT, PE, myocardial infarction (MI), and cerebral infarction. We also capture treatment “failures” noted as the need for anti-hemorrhagic rescue interventions such as topical agents (e.g., oxidized cellulose) and recombinant factor VIIa.

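### Continuous secondary outcomes get t tests and linear regression with no routine covariate, although center is a stratification factor and preoperative hemoglobin is in hand: valid, but less precise than it could be

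*Protocol article*

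**What the plan says.** All references are to the protocol article.

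- **Outcomes.** The Secondary outcomes section lists "estimated intraoperative blood loss, and change in hemoglobin" among others. Intraoperative blood loss is also the first secondary objective named under Objectives and research questions.
- **Methods for continuous outcomes.** Statistical methods says "Secondary analyses of the effect of tranexamic acid on the volume of intraoperative blood loss and the perioperative adverse event rate will follow" the approach of the primary analysis, "using chi-square or *t* tests, depending the outcome, and logistic or linear regression to estimate the magnitude of effect". No transformation, rank test or covariate is named. The sentence covers blood loss and adverse events; it does not mention change in hemoglobin.
- **Adjustment.** The only rule concerns the primary relative risk and depends on the data: "If notable baseline imbalances are present, an adjusted estimate will be derived for the RR by stratifying on the potential confounders".
- **Data in hand.** Preoperative hemoglobin defines a subgroup: "preoperative hemoglobin (< 100 g/L, 100–120 g/L, and > 120 g/L". It is also needed to form the change. The Randomization section stratifies by center, and thirteen centers have committed to take part.
- **Distribution of blood loss.** The Background says only that "median intraoperative blood loss is between 600 and 1700 mL". No mean, SD or shape is given.

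**The concern.** Linear regression on arm alone gives the same comparison as a two-sample t test, so planning a regression adds no precision until covariates are named. Two covariates suggest themselves, and both are already recorded.

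- **Center.** It is built into the randomization. Surgical practice can differ by center, and the published medians cited in the Background span almost threefold (1700/600 = 2.8). An analysis that leaves center out carries the between-center variation in its standard error, although the design has balanced it between arms.
- **Preoperative hemoglobin.** It predicts postoperative hemoglobin. An unadjusted change score subtracts all of the baseline value, whatever the correlation. Regression subtracts only the share that the data support.

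At stake are wider confidence intervals than necessary for two secondary outcomes that speak to how the drug works. A rule that adjusts only after a notable imbalance has been seen does not meet this: the gain comes from the covariate's relation to the outcome, not from imbalance, and it is there when the arms are balanced.

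**Working it through.** **The plan's own figure.** The sample size rests on 50% versus 35% transfused, 80% power and two-sided 5%. With pooled variance, the mean proportion is 0.425 and

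n per arm = [1.96·√(2·0.425·0.575) + 0.8416·√(0.5·0.5 + 0.35·0.65)]² / 0.15² = (1.370 + 0.582)² / 0.0225 ≈ 169.3, rounded up to 170, so 340 in total.

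The stated 354 equals 340/0.98² = 354.0. Both figures concern the binary primary outcome, and nothing below alters them. The article states no power or SD for blood loss or hemoglobin.

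**Hemoglobin: baseline-adjusted versus change score.** Assume equal variance σ² before and after surgery and correlation rho.

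- Variance of the change: 2σ²(1 − rho).
- Residual variance after regression on baseline: σ²(1 − rho²).
- Ratio: (1 − rho²) / [2(1 − rho)] = (1 + rho)/2.

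To put this in terms of power, take the true effect at which the unadjusted change score has 80% power with 177 per arm. The adjusted power is then Φ(2.8016/√[(1+rho)/2] − 1.96).

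| rho (assumed) | Variance ratio | Power, change score | Power, baseline-adjusted |
|---|---|---|---|
| 0.3 | 0.65 | 80% | 93.5% |
| 0.5 | 0.75 | 80% | 89.9% |
| 0.7 | 0.85 | 80% | 86.0% |
| 0.8 | 0.90 | 80% | 84.0% |
| 0.9 | 0.95 | 80% | 82.0% |

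The gain is 2 to about 14 points. It shrinks as rho approaches 1, and in large samples adjustment is not less precise than the change score at any rho.

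**Blood loss: center.** If center explains a share R² of the variance, the residual variance falls to about (1 − R²) of the unadjusted value. The price is 12 degrees of freedom (13 centers minus 1) out of 352 (354 minus 2). The article gives no between-center figure, so the gain cannot be put as a number.

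**Is the planned t test valid?** In simulated log-normal blood loss, 177 per arm, no true effect and coefficients of variation from 0.3 to 1.0, the raw-scale t test rejected in 4.3% to 5.2% of 10,000 trials per setting. It holds its level.

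**Would a log scale gain power?** Assume 20% lower loss and 177 per arm; shape and spread are assumptions too.

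| Assumed distribution | CV | Raw-scale t test | Log-scale t test |
|---|---|---|---|
| Log-normal, SD of log 0.6 | 0.66 | 89% | 93% |
| Log-normal, SD of log 0.7 | 0.80 | 75% | 84% |
| Log-normal, SD of log 0.8 | 0.95 | 62% | 75% |
| Gamma | 0.66 | 88% | 81% |
| Gamma | 0.80 | 73% | 59% |

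These are simulated values, good to about a percentage point or two. The order reverses with the assumed shape, although both shapes are right-skewed.

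**The case against.** **The article does not fix a t test for hemoglobin change.** This is correct. The sentence on secondary analyses does not name that outcome, and an unadjusted t test on it is only an inference from the general wording. The point is therefore limited to this: the outcome is listed, no baseline-adjusted analysis is stated, and the methods given for continuous outcomes carry no covariate.

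**Covariate lists are ordinary content of an analysis plan, which is not shown.** This stands in part. If that plan already adjusts for center and baseline hemoglobin, confirmation is all that is needed. But the article does set out a method for continuous secondary outcomes and an adjustment rule that acts only on observed imbalance. Even if that rule carries over from the primary relative risk to the secondary outcomes, the adjustment remains conditional.

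**A stronger reading is tempting:** that blood loss is skewed, so the t test is wrong or throws away power, and a log-scale analysis should replace it. The documents do not support this. A range of medians hints at skewness but says nothing of its size. The t test keeps its error rate at this sample size. The power advantage of the log scale appears under an assumed log-normal shape with a constant ratio, the setting that suits it best, and turns into a loss under gamma-distributed data. The log scale also changes the question, from a difference in mean mL to a ratio of geometric means. That is a trade-off, not a free gain.

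**Conclusion.** The point holds as a minor gain in efficiency. The planned analyses are valid, but for two secondary outcomes they leave unused information that the trial already has.

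For hemoglobin, adjustment lowers the variance by 35% at rho 0.3, 15% at rho 0.7 and 5% at rho 0.9. This rests on equal variances before and after surgery, on an assumed rho, and on the comparison being with an unadjusted change score, which the article implies at most. For blood loss, including center respects the stratified design; the direction of the gain is clear but its size is unknown.

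A reader might infer that the primary result or the sample size is affected. Neither is: the 340 and 354 patients concern the binary transfusion outcome, and the article claims no power for blood loss or hemoglobin.

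**What to change.** State the following in the analysis plan before unblinding, or confirm that it is already there:

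1. Blood loss: linear regression on arm and center, with the adjusted difference in mean mL and its 95% confidence interval as the estimate.
2. Hemoglobin: linear regression of the postoperative value, or of the change, on arm, preoperative hemoglobin (continuous) and center. With baseline in the model, both versions give the same treatment effect.
3. Both adjustments apply whether or not baseline imbalance is seen.
4. Optionally, a log-scale or other skew-robust analysis of blood loss as a sensitivity analysis, with medians by arm and no claim of a power gain.

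The cost is a few lines of wording. No new data, visits or patients are needed, and the estimates stay in mL and g/L. If some centers recruit very few patients, a rule for pooling them should be set in the same place.
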